# Effect of supervised exercise in groups on psychological well-being among pregnant women at risk of depression (the EWE Study): study protocol for a randomized controlled trial

**DOI:** 10.1186/s13063-017-1938-z

**Published:** 2017-05-05

**Keywords:** Pregnancy, Antenatal, Supervised exercise, Depression, Anxiety, Psychological well-being, Randomized controlled trial

## Abstract

**Background:**

Pregnant women with depression and/or anxiety prior to pregnancy are at higher risk of preterm birth, breastfeeding problems, postpartum depression, and disruption of the mother-infant attachment. It is well documented that exercise improves psychological well-being in nonpregnant subjects with symptoms of depression. However, in only a few small studies have researchers examined the effect of exercise on symptoms of depression among pregnant women. We hypothesize that physiotherapist-supervised group exercise for pregnant women at risk of antenatal depression increases their psychological well-being. This paper describes the study protocol of a randomized controlled trial (RCT) on a supervised group exercise intervention for pregnant women with a current or previous history of depression and/or anxiety.

**Methods/design:**

The RCT is being carried out at the Department of Obstetrics, Rigshospitalet, Copenhagen University Hospital, in the period 2016–2019. The inclusion criteria are pregnant women ≥18 years of age with depression and/or anxiety requiring treatment by a psychiatrist or a psychologist within the last 10 years and/or intake of antidepressants in the 3 months prior to conception and/or during pregnancy. The women must have appropriate Danish language skills, be pregnant with a single fetus, give written informed consent, and be at 17–22 gestational weeks when the intervention begins. The primary outcome is psychological well-being (the five-item World Health Organization Well-being Index). Secondary outcomes are symptoms of depression (Edinburgh Postnatal Depression Scale), functional ability (General Health Questionnaire), clinical symptoms of anxiety (State-Trait Anxiety Inventory), sleep quality and sleep disturbances (Pittsburgh Sleep Quality Index), and pregnancy and delivery outcomes. The intervention is supervised group exercise twice weekly for 12 weeks. The control group will receive standard antenatal care. On the basis of sample size calculation, a total of 300 women will be randomly assigned to either the intervention or the control group in a ratio of 1:1.

**Discussion:**

The trial is expected to contribute to the body of knowledge used in planning antenatal care for pregnant women at risk of depression.

**Trial registration:**

ClinicalTrials.gov, NCT02833519. Registered on 19 May 2016.

**Electronic supplementary material:**

The online version of this article (doi:10.1186/s13063-017-1938-z) contains supplementary material, which is available to authorized users.

## Background

Mental illness affects individuals’ functioning, resulting in emotional suffering and reduced quality of life for the affected persons as well as social and economic consequences for society [1]. A reduction in mental illness is of great importance for public health [2], and the World Health Organization (WHO) has emphasized this by giving greater attention to the prevention of mental illness and the promotion of mental health in health care systems [1]. Among other initiatives, the WHO has taken an initiative to unite knowledge and forces across national borders to reach consensus regarding which activities would be appropriate to increasing the quality of mental health care, including specific steps to be taken [1].

Maternal depression and anxiety are the most common psychiatric disorders during pregnancy and in the postpartum period [3]. A systematic review based on 28 studies done in a wide range of developed countries estimated the prevalence of antenatal depression to range from 6.5% to 12.9% and the prevalence of depression during the first 3 months postpartum to be up to 19% [4]. Antenatal anxiety is reported in 4% to 39% of all pregnant women and in up to 16% of all women in the postpartum period [5].

The consequences of depression and anxiety in the antenatal and postnatal period are extensive [6–13]. Women with antenatal depression have an increased risk of preterm birth [6] and postpartum depression [7], as well as a lesser likelihood of breastfeeding initiation [6]. Antenatal and postnatal depression is associated with disruption of the mother-infant relationship [8, 9], developmental delays in childhood [10], and behavior problems such as low adaptive functioning and social competence in childhood and adolescence [11, 12]. Antenatal anxiety is associated with an increased risk of low birth weight [13] and increased risk of attention and hyperactivity problems, as well as other behavioral and emotional challenges, in childhood [14, 15].

The strongest risk factor for antenatal depression and anxiety is a history of depression and/or anxiety prior to pregnancy [16]. About 20% of women with a history of depression prior to pregnancy experience recurrent major depression during pregnancy or postpartum, and 56% of women with anxiety prior to pregnancy experience anxiety in this period. Among women with comorbid depression and anxiety prior to pregnancy, 29% report a recurrent major depressive episode, and as many as 63% experience anxiety during pregnancy and the postpartum period [16].

The major challenges outlined have led to both national and international guidelines recommending a coordinated care plan for this group of pregnant women [17, 18]. This plan is recommended to include screening and treatment for depression and anxiety as part of routine antenatal care, including interdisciplinary and intersectoral teamwork with obstetricians, psychiatrists, psychologists, social workers, nurses, and midwives [17, 18].

Randomized studies have shown that exercise among clinically depressed patients has a positive effect on signs of depression and anxiety [19]. However, until now, in very few studies have researchers examined the effects of exercise in the prevention of or treatment for symptoms of depression and anxiety among pregnant women. According to a meta-analysis by Daley et al. [20], there is some evidence that exercise may be effective in treating antenatal depression, but as the authors point out, this conclusion is based on trials with low to moderate methodological quality and on a small meta-analysis sample size. Their meta-analysis also concluded that more high-quality trials are needed to examine whether exercise is effective in treating signs of depression during pregnancy.

The Effect of Group Exercise on Mental Wellbeing among Pregnant Women at Risk of Perinatal Depression trial (EWE Study) is a large randomized controlled trial (RCT) using supervised exercise in groups twice weekly for 12 weeks as an intervention for pregnant women at risk of depression and anxiety. The intervention period is 12 weeks because a major meta-analysis based on 49 studies of exercise and depression found that a training period of 10–16 weeks had the best effect on symptoms of depression [19]. Supervised exercise in groups was chosen because pregnant women experience a sense of security when they exercise together in professionally led sessions where the professional can monitor the extent of the physical exercise and provide guidance [21].

### Objective

The aim of this RCT is to assess whether a supervised group exercise intervention increases psychological well-being in pregnant women with a current or previous history of depression and/or anxiety. This paper describes the design of the study.

## Methods/design

### Study design

The EWE Study is a parallel-group RCT designed to evaluate the effect of supervised exercise in groups on psychological well-being among pregnant women with a current or previous history of depression and/or anxiety. The EWE Study was designed in accordance with the Consolidated Standards of Reporting Trials (CONSORT) recommendation for RCTs [22] and with the Standard Protocol Items: Recommendations for Interventional Trials (SPIRIT) guidelines for reporting trial protocols (Additional file 1) [23].

### Study setting

Participants will be recruited among pregnant women attending antenatal care at the Department of Obstetrics, Rigshospitalet, Copenhagen University Hospital, Copenhagen, Denmark. This hospital serves as a primary birth facility for women from the city of Copenhagen, as well as being a tertiary referral center, with 5672 deliveries in 2015. The intervention will take place at Rigshospitalet, Copenhagen University Hospital.

### Inclusion criteria

Eligible participants will be pregnant women ≥18 years of age with depression and/or anxiety requiring treatment by a psychiatrist or a psychologist within the last 10 years and/or intake of antidepressants in the 3 months prior to conception and/or during pregnancy. The women must have appropriate Danish-language skills, be pregnant with a single fetus, give written informed consent, and be at 17–22 gestational weeks when the intervention begins. Pregnant women who fulfill the inclusion criteria but have a chronic disease are included in the study only after prior agreement with an obstetrician. Chronic disease refers to a diagnosis where signs, symptoms, and treatment imply an expected long duration and lack of cure, such as certain types of heart disease and diabetes [24].

Depression in this study covers the *Diagnostic and Statistical Manual of Mental Disorders, Fifth Edition* (DSM-5), criteria of disruptive mood dysregulation disorder, major depressive disorder, persistent depressive disorder (dysthymia), bipolar disorder, and unspecified depressive disorder [25]. Anxiety in this study covers the DSM-5 criteria of separation anxiety disorder, specific phobia, social anxiety disorder, panic disorder, agoraphobia, generalized anxiety disorder, and obsessive compulsive and related disorders [25].

### Exclusion criteria

Potential participants will be excluded from participation for the following reasons: age <18 years, multiple pregnancies, substance abuse problems, eating disorders, pelvic girdle syndrome (diagnosed by a physiotherapist or medical doctor) in the current or a previous pregnancy, fetal malformations (diagnosed by ultrasound), fetal chromosomal disorder, or severe obstetric or medical complications.

### Withdrawal

Participants will be withdrawn from the study after randomization if they meet one or more of the following criteria: an occurrence of pelvic instability, preeclampsia, vaginal bleeding, or symptoms of preterm labor contraindicating physical activity.

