### Sample size estimation

The sample size estimation is based on the primary outcome—psychological well-being—measured by the WHO (Five) Well-being Index (WHO-5) [27]. A sample size calculation was carried out to detect a 10-point higher score on the WHO-5 at 29–34 weeks of gestation in the intervention group compared with the control group. A 10-point difference in the WHO-5 score between the intervention and control groups is considered clinically significant [28, 29], and an SD of 16 was used. This SD is based on a previous assessment of the WHO-5 score in a population of 3970 pregnant women with and without mental disorders measured at 10–12 weeks of gestation in the total population of pregnant women at Rigshospitalet, Copenhagen University Hospital. This SD value (16 points) was used in the sample size calculation because we did not have an SD in the WHO-5 score measured at 29–34 weeks at our disposal. We expect 50% of the participants to follow the program for at least 75% of the sessions (high participation, 19–24 sessions), whereas 35% will participate in 50% to 75% of the sessions (moderate participation, 12–18 sessions) and 15% will engage in less than half of the sessions (low participation). We expect high participation in the exercise intervention to lead to an increase of 10 points in the WHO-5 score, moderate participation to lead to an increase of 7 points, and low participation to lead to an increase of 2 points compared with the control group. This will lead to the intervention group’s having an average value 7.75 points (0.50 × 10 + 0.35 × 7 + 0.15 × 2) higher than that of the control group at 29–34 weeks of gestation. With a power of 90% and a two-sided significance level of 5%, a difference in well-being level of 7.75 points (SD 16) in the two groups at 29–34 weeks of gestation can be detected by a two-sample *t* test with 91 patients in each group.

We expect that it will be necessary to include a total of 300 pregnant women because we anticipate that 13% (20 women) in each group will drop out as a result of discomfort or complications related to pregnancy and that 39 women (30%) of the remaining 131 participants in each group will not answer the questionnaire at 29–34 weeks of gestation, leaving 91 participants in each group.

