*Sleep quality and sleep disturbances*, measured by the Pittsburgh Sleep Quality Index (PSQI). The PSQI is a subjective scale measuring sleep quality and sleep disturbances over a 1-month period [43]. The scale addresses quantitative aspects of sleep, such as sleep latency and sleep duration, as well as more subjective aspects, such as restfulness of sleep [43]. Overall sleep quality is measured by means of 19 questions, and the total score is based on 7 “component” scores, each of which has a range of 0–3 points. A score of 0 indicates no difficulty, whereas a score of 3 indicates severe difficulty. The sum of the component scores results in a “global” score ranging from 0 to 21 points, where 21 indicates severe sleep problems. The PSQI has been found to be useful in pregnancy research, and good internal consistency and construct validity have been reported [44].
*Pregnancy and delivery outcomes*, comprising sick leave (measured in days), hospitalization (measured in number of hospital admissions and days), labor onset (spontaneous or induced), use of epidural anesthesia during delivery (yes or no), duration of labor (measured in hours), mode of delivery (percentage of participants with spontaneous delivery, vacuum extraction, or cesarean section), birthweight (measured in kilograms), and birth length (measured in centimeters). This information will be obtained from patient records.

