### Data analysis

The primary data analysis will be performed on the basis of the intention-to-treat principle. We will compare baseline data for the two groups with Student’s *t* test, the chi-square test, or nonparametric tests. It is anticipated that a large proportion of values for the outcome variable will be missing, owing to dropout and nonresponse to the questionnaire. These data will be assumed missing at random, and therefore observed patient characteristics will be used to impute missing data by means of multiple imputation. Because it is expected that there will be a dropout rate of 13% (20 women) in each group and that some women will participate in the group training only a few times, in addition to the intention-to-treat analyses, we will perform a per-protocol analysis of the women who perform ≥75% of all training sessions.

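### Withdrawing women from the study, not only from exercise, for pregnancy complications after randomization weakens the intention-to-treat analysis

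*Protocol article*

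**What the plan says.** The Withdrawal section of the protocol article gives an active rule: "Participants will be withdrawn from the study after randomization if they meet one or more of the following criteria". The criteria are "an occurrence of pelvic instability, preeclampsia, vaginal bleeding, or symptoms of preterm labor contraindicating physical activity". The rule names the study, not the exercise sessions, as what the woman leaves. It is not limited to the exercise arm, and no other section says that follow-up continues.

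The Sample size estimation section fits that reading: "we anticipate that 13% (20 women) in each group will drop out as a result of discomfort or complications related to pregnancy". It applies nonresponse only to those who are left: "39 women (30%) of the remaining 131 participants in each group will not answer the questionnaire".

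The Data analysis section states: "The primary data analysis will be performed on the basis of the intention-to-treat principle". It also says: "It is anticipated that a large proportion of values for the outcome variable will be missing, owing to dropout and nonresponse to the questionnaire". Under an assumption of missing at random, "observed patient characteristics will be used to impute missing data by means of multiple imputation".

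Under Secondary outcomes, the pregnancy and delivery outcomes (among them admissions, labor onset, mode of delivery and birthweight) come from patient records. The article does not say whether the records of withdrawn women are still used.

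**The concern.** A contraindication to physical activity explains why sessions stop. It does not explain why an emailed questionnaire or the reading of an existing record should stop, least of all in the control arm, where there are no sessions to end.

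The events occur after randomization and exercise may affect them. An intention-to-treat comparison needs outcomes from all randomized women whatever happens to them later. Here the protocol itself creates missing values, for a reason tied to the woman's health, and then has to model them. Two things are at stake: the primary comparison of WHO-5 at 29–34 weeks, and the delivery outcomes, which are where complications of this kind would show.

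**Working it through.** **1. The plan's own figures.** All inputs are from Sample size estimation.
- Expected difference: 0.50 × 10 + 0.35 × 7 + 0.15 × 2 = 7.75 points; SD 16; two-sided 5%; power 90%.
- A two-sample t test needs 90.54, so 91 per arm, as stated. Power with 91 is 90.1%.
- Attrition: 91 / 0.70 = 130, and 130 / 0.87 = 149.4, so 150 per arm and 300 in total, as stated.
- The article's 131 and 39 do not subtract exactly (150 − 20 = 130; 131 − 39 = 92). This is rounding (0.87 × 150 = 130.5) and has no consequence.

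**2. What the order of subtraction implies.** The plan computes (150 − 20) × 0.70 = 91. If it expected T2 answers from the 20 women at the same response rate, it would have 150 × 0.70 = 105. The plan therefore counts on no T2 questionnaire from 20/150 = 13.3% of each arm. As a measure of the withdrawal rule this is an upper bound on the planned loss, for two reasons. The 20 include women who leave because of discomfort, which is not a withdrawal criterion. The rule also has no time limit, and an event after T2 costs no primary outcome.

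**3. Size of a possible bias (illustration).** Assumptions: exercise has no effect; a share c = 20/150 of both arms has a complication; these women score g points lower on the WHO-5, with g from 5 to 15; a share q of an arm is withdrawn, all from among these women. Relative to women without complications, the mean of those who remain is −g × (c − q)/(1 − q). The bias is the exercise mean minus the control mean, with q = 20/150 in the exercise arm, so that the exercise mean is 0.

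| Withdrawn, control arm | (c − q)/(1 − q), control | Bias, g = 5 | g = 10 | g = 15 |
|---|---|---|---|---|
| 20/150 | 0 | 0 | 0 | 0 |
| 10/150 | 10/140 = 0.071 | 0.36 | 0.71 | 1.07 |
| 0 | 20/150 = 0.133 | 0.67 | 1.33 | 2.00 |

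Positive values favor exercise. They describe a comparison of the women who remain. Imputation that carries no information on the complication would leave much the same bias.

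Equal withdrawal rates do not settle the matter if exercise changes the events. Suppose complications occur in 10/150 of the exercise arm and 20/150 of the control arm, and all these women are withdrawn. The part of the benefit that comes from fewer complications, g × 10/150 = 0.33 to 1.00 points, is then absent from both the observed data and the comparison.

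**4. What imputation can do.** Imputation borrows T2 values from women similar to those who are missing. If the rule is followed, women with a listed event before T2 have few or no T2 values. Even if the event entered the imputation model, there would be hardly any outcomes from which to estimate its effect, and the imputed values would largely reflect women without complications.

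**5. Delivery outcomes.** These need no questionnaire. With record extraction for everyone, up to 150 per arm are available. If extraction ends at withdrawal, about 130 remain, and the missing women are those with complicated pregnancies or discomfort.

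**The case against.** The strongest reply is that the plan foresees dropout and imputes the missing values within the intention-to-treat analysis. The per-protocol analysis is an addition to it. A reader might infer that the withdrawal rule breaks the intention-to-treat analysis outright. The text does not support that, because withdrawn women can stay in the analysis set through imputation. The imputation inputs are observed patient characteristics, not baseline data only, and the detailed model may stand in an analysis plan that is not shown. This stands: the analysis is weakened, not abandoned. It does not remove the problem in step 4, which comes from the absence of observed outcomes and not from the choice of predictors.

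Other tempting readings also go too far.
- **Delivery outcomes are lost.** No section says that record extraction stops. The wording implies it at most, and the flow diagram (Fig. 1) could not be read for this review. The complications in the rule are not themselves listed as outcomes, and the Discussion promises safety data for the intervention group, so it cannot be said that harm is hidden. Those safety data are promised for one arm only and so do not give a comparison.
- **The rule removes 13% of each arm.** As step 2 shows, this is an upper bound on the planned loss.
- **Complications are detected more often in the exercise arm.** Twice-weekly contact with physiotherapists in an unblinded trial makes this plausible, but the documents do not show it. The plan expects equal loss in both arms, and both arms receive more frequent and longer consultations under standard care.
- **Retention raises power.** This depends on assumptions. With 105 per arm and the full 7.75 points, power is 93.7%. If the retained women gain nothing from exercise, the difference is 7.75 × 0.87 = 6.74 points and power with 105 is 86.0%, below the 90.1% for 91 women at 7.75 points. If none of the 20 answer, the number stays at 91. No power gain is claimed.

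**Conclusion.** The concern holds in a limited form. The withdrawal rule, read with the sample size section, creates avoidable missing primary outcomes that depend on health after randomization. It leaves the intention-to-treat analysis to an assumption of missing at random that the rule itself makes hard to defend. The planned loss from this source is at most 20 of 150 women per arm.

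Bias arises mainly if withdrawal differs between arms or if exercise affects the listed events. Under the assumptions in step 3 it is zero with equal withdrawal and no exercise effect, and 0.4 to 2.0 points in favor of exercise with unequal withdrawal, against a planned difference of 7.75 points. The 5 to 15 point deficit and the unequal rates are assumptions; the documents give no figures for either. The effect on delivery outcomes is conditional on record extraction ending at withdrawal. The reason to act is validity, not power.

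**What to change.** Reconcile the Withdrawal, Sample size estimation, Secondary outcomes and Data analysis sections, and leave the clinical criteria for stopping exercise as they are.
- State that the listed events end only the exercise sessions.
- State that all randomized women in both arms continue to receive the T2 and T4 questionnaires, and have delivery data taken from records, unless they withdraw consent.
- Analyse all women in the arm to which they were randomized.
- Report discontinuation of exercise by reason.

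The cost is a change of wording and slightly more follow-up work. Questionnaires go out as emailed links and delivery data come from existing records, so no visit is added. The intention-to-treat effect may be somewhat diluted by women who stopped exercising. The change is best made while recruitment is open, because T2 answers that were not collected cannot be recovered later.
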